## Abstract

**Background:**

Oxytocin is an effective drug for induction of labour, but is associated with serious adverse effects of which uterine tachysystole, fetal distress and the need of immediate delivery are the most common. Discontinuation of oxytocin once the active phase of labour is established could reduce the adverse effects.

The objective is to investigate how the caesarean section rate is affected when oxytocin stimulation is discontinued in the active phase of labour compared to labours where oxytocin is continued.

**Methods:**

CONDISOX is a double-blind multicentre randomised controlled trial conducted at Danish and Dutch Departments of Obstetrics and Gynaecology. The first participant was recruited on April 8 2016.

Based on a clinically relevant relative reduction in caesarean section rate of 7%, an alpha of 0.05, a beta of 80%, we aim for 1200 participating women (600 in each arm).

The CONDISOX trial includes women at a gestational age of 37–42 complete weeks of pregnancy, who have uterine activity stimulated with oxytocin infusion for the induction of labour. Women are randomised when the active phase of labour becomes established, to study medication containing either oxytocin (continuous group) or placebo (discontinued group) infusion. Women are stratified by birth site, indication for oxytocin stimulation (induction of labour, prelabour rupture of membranes) and parity (nulliparous, parous +/− previous caesarean section).

We will compare the primary outcome, caesarean section rate, in the two groups using a chi-square test with a *p*-value of 0.05. If superiority is not demonstrated, we have a pre-defined post hoc non-inferiority boundary (margin, delta) at 1.09.

Secondary outcomes include duration of the active phase of labour, incidence of uterine tachysystole, postpartum haemorrhage, admission to the neonatal intensive care unit, Apgar score, umbilical arterial blood pH, and birth experience.

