### Randomisation, blinding and informed consent

Women will be informed of the trial when induction of labour is planned or at the first visit to the labour ward in case of prelabour rupture of membranes. Subjects’ signed informed consent to participation will be obtained prior to randomisation and intervention (i.e. before any oxytocin stimulation).

Women will be randomised in a 1:1 ratio to either the continued oxytocin group or the discontinued oxytocin group using an Internet-based randomisation programme (Trialpartner). Random block-sizes of four will be used, and the women will be stratified by site, parity (nulliparous or parous +/− previous caesarean) and indication for oxytocin infusion (induction of labour or induction due to prelabour rupture of membranes (PROM)). The randomisation number generated by the computer programme corresponds to number of the studymedication (masked, identical ampoules). The personnel of the delivery ward will administer the medication according to existing guidelines concerning administration [5, 12, 13]. Women, caregivers, and trialmanagers will be blinded to the allocation due to the use of identical study medication preparations.

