### Side effects and risks

We expect a rate of persistent failure to progress of 8–46% among the participants in the discontinued group versus 3–17% in the continued group [1–4]. Based on data from the pilot study [9], we expect a caesarean section rate of 15% in the discontinued group versus 22% in the continued group. According to the pilot study and previous studies [1–4], maternal and neonatal complications in the discontinued group are expected to be lower than in the continued group (The 2018 data for labour that are induced in Denmark indicate an acute caesarean section rate of 14.6%. However, the latter figure includes women who respond to prostaglandin alone and there are no data for women who require oxytocin infusion in addition).

All women will be monitored with continuous electronic fetal heart rate monitoring during labour to detect complications such as uterine tachysystole and non-reassuring/pathological fetal heart rate in accordance with national guidelines. Women and their newborns will be observed for at least 3–6 h postpartum (termination of study medication) according to the current practice on the delivery ward before discharged home.

Delivery ward staff is responsible for timely reporting of any adverse reactions to the trial manager.

Adverse reactions/events will be registered immediately in the electronic medical file of the patient. The Summary of Product Characteristics (SPC) of *Syntocinon®* will be used as reference [6] to determine whether a Serious Adverse Reaction is expected or unexpected. The primary investigator or a nominated deputy will go through the participants’ electronic medical record 7–30 days postpartum during data collection. The primary investigator will ensure that all relevant information about suspected serious unexpected adverse reactions that are fatal or life threatening is recorded. The primary investigator will report as soon as possible (and in any case no later than seven days) to the competent authorities concerned. The primary investigator will ensure that any relevant follow-up information is subsequently communicated within an additional eight days.

The primary investigator will report to the competent authorities concerned and to the Ethics Committees all other suspected unexpected serious adverse reactions as soon as possible but within a maximum of 15 days of first knowledge.

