### Power calculation and statistical analysis

Based on the pilot study [9] we expect a caesarean section rate of 22% in the continued group. A clinically relevant relative reduction in the caesarean section rate would be 30%, corresponding to a caesarean section rate of 15% in the discontinued group. Aiming for a power (beta) of 80% and an alpha of 0.05, superiority can be shown with a sample size of 482 women in each group. Allowing for crossover and a dropout of 5% we aim to recruit a total of 600 women per treatment arm (1200 in total).

If superiority of oxytocin discontinuation vs. continued oxytocin stimulation for the reduction of the incidence of caesarean section cannot be shown, non-inferiority testing is a relevant alternative. It is plausible that improvements in secondary outcomes will be seen, even if there is no superiority on the primary outcome. To allow formal non-inferiority testing as an alternative, we define a post hoc non-inferiority boundary (margin, delta) at 1.09. This boundary is to exclude a rate of 22% in the continued oxytocin group as compared to 24% in the discontinued group.

Data will be analysed according the intention-to-treat principle. Basic demographic data will be presented with counts and percentages for categorical variables, mean and standard deviation for continuous Gaussian distributed variables, and median and interquartile range for continuous non-Gaussian variables. The primary outcome variable will be assessed by comparing the event rates in the two groups using a chi-square test with a significance threshold *p*-value of < 0.05. Results will be presented as absolute and relative risks along with 95% confidence intervals (Cl) and the numbers needed to treat (if applicable). Categorical secondary outcomes will be assessed in the same way as the primary outcome. For continuous secondary outcomes with a Gaussian distribution (following log transformation if appropriate) we will assess differences between groups using the student’s t-test, and with a non-parametric Mann-Whitney U test if the data are non-Gaussian. We will present time to delivery using Kaplan-Meier estimates and survival curves, and test the differences between the two groups using the log-rank test. We will use multivariate logistic regression with adjustment for indifferences in baseline characteristics to calculate odds ratios with 95% confidence intervals.

Subgroup analysis will be undertaken for the following subgroups:

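### The abstract gives the design effect as a 7% relative reduction with a beta of 80%; the 482 and 600 per arm rest on 22% versus 15% (7 percentage points, about 32% relative) at 80% power

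*Protocol article*

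**What the plan says.** The article states the design effect in two places.

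- **Abstract, Methods.** "Based on a clinically relevant relative reduction in caesarean section rate of 7%, an alpha of 0.05, a beta of 80" per cent, leading to 1200 women, 600 per arm. No caesarean rate is given for either arm.
- **Power calculation and statistical analysis.** "Based on the pilot study [9] we expect a caesarean section rate of 22% in the continued group". Then: "A clinically relevant relative reduction in the caesarean section rate would be 30%, corresponding to a caesarean section rate of 15% in the discontinued group". The calculation follows: "Aiming for a power (beta) of 80% and an alpha of 0.05, superiority can be shown with a sample size of 482 women in each" (arm). This is raised to 600 per arm for crossover and 5% dropout.

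The section on side effects and risks repeats the pair of rates: "we expect a caesarean section rate of 15% in the discontinued group versus 22% in the continued group". The Background reports the same two percentages as the pilot result.

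**The concern.** Both places use the word relative for the quantity that justifies the same 1200 women, yet one says 7% and the other 30%. They cannot both be right. Both places also attach the name beta to 80%. Beta is the type II error, so the abstract taken literally describes a trial with 20% power.

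The target difference and the power are what a reader uses to interpret a superiority test that fails. The article plans for that outcome: it sets a fallback non-inferiority margin of 1.09, a ratio, which it explains as 22% versus 24%. In the abstract a 7% relative reduction therefore stands close to a margin that allows a 9% relative increase. A reader of the abstract alone could conclude that the trial was sized for effects of that order, and could take a null result as evidence against a 7% relative benefit. The abstract gives no base rate from which to notice the slip.

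**Working it through.** **Inputs.** The continued-group rate of 22%, the discontinued-group rate of 15%, alpha 0.05, power 80% and 482 per arm come from the power section. Allocation is equal ("Women will be randomised in a 1:1 ratio"). Sidedness is not stated. I assume a two-sided test, in keeping with the planned analysis ("using a chi-square test with a significance threshold").

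**Formula** (normal approximation, pooled variance under the null, no continuity correction), with p̄ = (p1 + p2)/2:

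n per arm = [1.960·√(2p̄(1−p̄)) + 0.842·√(p1(1−p1) + p2(1−p2))]² / (p1−p2)²

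**Step 1: reproduce the plan's figure, 22% versus 15%.**
- p̄ = 0.185, and 2p̄(1−p̄) = 0.30155.
- p1(1−p1) + p2(1−p2) = 0.1716 + 0.1275 = 0.2991.
- Numerator: (1.0763 + 0.4603)² = 2.361. Denominator: 0.07² = 0.0049.
- n = 481.8, so **482 per arm**, as stated. Power is 80.0% at 482 and 87.8% at 600.
- A one-sided test would need 380, and a two-sided test with continuity correction 511. The two-sided uncorrected reading is the one that matches.

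**Step 2: express that difference both ways.**
- Absolute: 22 − 15 = 7 percentage points.
- Relative: 7/22 = 31.8%.

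The abstract's 7 is the absolute difference.

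**Step 3: take the abstract literally.** The base rate of 22% has to be borrowed from the power section.
- 0.93 × 22% = 20.46%, a difference of 1.54 points.
- p̄ = 0.2123, 2p̄(1−p̄) = 0.33446, and the sum of the two variances is 0.33434.
- Numerator: (1.1335 + 0.4866)² = 2.625. Denominator: 0.0154² = 0.00023716.
- n = **11,068 per arm**, and 11,068/482 is about 23 times the stated figure.
- Power is 8.4% at 482 per arm and **9.5% at 600**.

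**Step 4: test the 30%.**
- 0.70 × 22% = 15.4%, which is 15% to the whole per cent, the precision used for the rates in that section.
- With 15.4% carried exactly, the formula gives 547 per arm. Power is 74.9% at 482, 81.6% at 570 (600 less 5%) and 83.5% at 600.

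**The case against.** The strongest defence is that the intended effect is never in doubt for someone who reads the whole article. The pair 22% and 15% appears in the Background, the risks section and the power section, and the 482 is exactly right for it. On this view the abstract contains one wrong adjective, the beta label is clear from context, and a null result would be read from the planned risks and 95% confidence intervals. Most of this stands: the calculation is sound. But the abstract still states a wrong figure for the primary design effect, and its reader has no rates from which to correct it. That the article condenses a fuller protocol does not excuse a contradiction within the article.

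Three stronger readings are tempting, and the document does not support them.

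- *That there are three incompatible design effects.* The power section ties 30% to 15% in a single sentence. The 30% is a loose rounding of 31.8%, not a separate target.
- *That the methods claim 80% power which 482 per arm does not deliver.* The 74.9% belongs to 22% versus 15.4%, a pair that the document never states. For the two rates that it names, 482 gives 80.0%.
- *That the trial is far too small.* The 11,068 shows that the word relative is wrong. It is not a requirement of this design.

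**Conclusion.** The abstract's design statement is wrong in two of its parameters. The 7% is an absolute reduction in percentage points, not a relative one, and the 80% is power, not beta. Against the 22% base rate, the literal statement would call for about 11,070 women per arm, and the planned 600 would miss such an effect about nine times in ten. A null superiority result from this trial says little about a 7% relative benefit and should not be read against it.

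The power section has two lesser faults: 30% where about 32% is meant, and the same beta label. The 482 and the 600 per arm are not in question.

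This rests on a two-sided test, which the document does not state but which reproduces 482 exactly, and on taking the base rate for the abstract's effect from the power section.

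**What to change.** - **Abstract, Methods.** State the basis as *an absolute reduction of 7 percentage points (22% to 15%, a relative reduction of about 32%), two-sided alpha 0.05, power 80% (beta 20%)*. The sponsor should confirm that the test is two-sided.
- **Power calculation and statistical analysis.** Replace 30% by *about 32%*, and give the power as *power of 80% (beta 20%)*.

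Keeping 30%, changing the rate to 15.4% and restating the requirement as 547 per arm is not a good alternative. It would change the design basis of a trial that has recruited since April 2016. It would also leave almost no room for the crossover that the plan allows for. If crossover c dilutes the effect so that the effective size is 570·(1−c)² (an assumption), 547 is met only when c is at most 1 − √(547/570), about 2%.

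The cost is a wording correction in two places. Sample size, recruitment and the planned test do not change.

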**Discussion:**

The high frequency of oxytocin use and the potential risks of both maternal and fetal adverse effects of oxytocin emphasise the need to determine the optimal oxytocin regime for induction of labour.

**Trial registration:**

NCT02553226 (registered September 17, 2015). Eudra-CT number: 2015–002942-30.

**Electronic supplementary material:**

The online version of this article (10.1186/s12884-019-2461-x) contains supplementary material, which is available to authorized users.

## Background

Syntocinon® (synthetic oxytocin) is one of the most widely used medications in obstetrics for induction of labour. In Denmark 2018, 27% nulliparous (8065 of 29,414) and 21% parous women (6636 of 31,502) had labour induced. Nearly half of these women received oxytocin stimulation as a single treatment method, or in combination with other methods (http://end2019.esundhed.dk/sundhedsregistre/MFR/Sider/MFR06A.aspx). Despite the extensive use of oxytocin only a few studies have focused on the duration of the infusion. There is no consensus as to whether oxytocin should be continued until delivery or discontinued after the onset of the active phase of labour [1–4].

The current regimen for induction of labour with oxytocin described in the national Danish Society of Obstetrics and Gynaecology (DSOG) guidelines [5] recommends that the infusion continues until delivery, unless complications (e.g. uterine tachysystole) occur, at which point the infusion rate is reduced or discontinued.

Although oxytocin is used in a high proportion of labours, its use is associated with adverse effects. The most frequent complication is uterine tachysystole [6], which increases the risk of fetal distress and birth asphyxia, requiring instrumental delivery or caesarean section. A less frequent but serious adverse event associated with the use of oxytocin is uterine rupture [7]. It is well established that oxytocin administration during labour causes a persisting down regulation of the oxytocin receptors [7], which persists postpartum and increases the risk of postpartum haemorrhage. Furthermore, initiation and duration of breastfeeding may also be adversely affected in women who undergo oxytocin stimulation [8].

We conducted a pilot study to investigate the effects of discontinued oxytocin infusion in the active phase of labour compared to continued oxytocin infusion on labour outcomes [9]. Between 2009 and 2011, two hundred women admitted for induction (188 cases) or augmentation of labour (12 cases) at the Regional Hospital of Randers were randomised to continued or discontinued oxytocin once the active phase of labour was established. The total caesarean section rate (secondary pre-specified outcome) for the oxytocin-discontinued group was 15% compared to 22% in the continued group, which was a non-significant reduction (*p* = 0.39). However, in the discontinued group, there were statistically significant fewer cases of postpartum haemorrhage, uterine tachysystole, and non-reassuring fetal heart pattern [9].

A recent published Cochrane review [10] concluded that discontinuation of oxytocin stimulation when the active phase of labour is established may reduce the caesarean section rate. However, the quality of evidence of the included trials was low, and when the analysis was restricted to results from participants who actually reached the active phase of labour, there was little or no difference on the caesarean section rate between the two groups.

### Objectives

The objective is to investigate how the caesarean section rate is affected when oxytocin stimulation is discontinued in the active phase of induced labour compared to labours where oxytocin is continued.

The incidence of other maternal and neonatal complications will be accessed as secondary outcomes.

## Methods

CONDISOX is a double-blinded multicentre randomised controlled trial conducted at Danish and Dutch Departments of Obstetrics and Gynaecology with approximately 24,000 annual births.

#### Study dates

The first participant was recruited the 8th of April 2016. The anticipated date of recruitment completion is February 2020.

#### Participants

The CONDISOX trial will include women at 37–42 complete weeks of gestation stimulated with oxytocin infusion for induction of labour (with or without cervical priming by prostaglandin).

Exclusion criteria are as follows:
Age < 18 yearsUnable to give written informed consentCervical dilation more than 4 cm when stimulation is initiatedMultiple pregnanciesNon-vertex presentationPersistent pathological cardiotocography (CTG) before oxytocin infusionEstimated fetal weight of more than 4500 g.

Figure 1 shows the study flow as outlined by the CONSORT (CONsolidated Standards Of Reporting Trials).

**Fig. 1 Fig1:**
[figure not shown]
Flowchart

### Oxytocin stimulation protocol

Standard procedures will be followed prior to stimulation [11, 12]

Stimulation will be given according to national Danish [5] and Dutch [13] guidelines. The guidelines and the obstetrical care are comparable between the two countries. Intravenous infusion of 10 IU Syntocinon® diluted in 1000 ml of isotonic saline (Denmark) or 5 IU Syntocinon® diluted in 50 ml of isotonic saline (The Netherlands) is initiated at 3.3 mIU/minute and increased every 20 min by 3.3 mIU/minute until regular contractions (three to five contractions every 10 min) are achieved. The maximal dose of infusion is 30 mIU/minute.

Women will be included in the study when the active phase of labour becomes established. The definition of the active phase of labour is in accordance with latest ACOG guideline [14]: complete effacement, cervical dilatation ≥6 cm, ≥3 contractions per 10 min, and rupture of membranes. Randomisation will be performed, and the infusion will be replaced by the study medication, which will be either *Syntocinon®* at the same concentration, or a placebo infusion with saline:
Denmark: Continued group; 10 IE *Syntocinon®* diluted in 1000 ml 0.9% NaCl infusion; discontinued group; 1 ml 0.9% NaCl diluted in 1000 ml 0.9% NaCl infusion. (prepared by the pharmacy in ampoules identified only by study number)The Netherlands: Continued group; 5 IU Syntocinon® diluted in 50 ml 0.9% NaCl infusion, discontinued group; 50 ml 0.9% NaCl. (Infusions are prepared by the pharmacy and identified only by study number).

### Outcome measures

#### Primary outcome

Caesarean section rate

#### Secondary outcomes

Maternal: Mode of delivery, indication for caesarean section or instrumental delivery, duration of the active phase of labour (from time of randomisation to delivery), total duration of labour from time of initiation of oxytocin stimulation until delivery, duration of time from admission to the delivery ward to delivery, incidence of uterine tachysystole, use of epidural analgesia, the total dosage of and duration of oxytocin infusion, rate of pyrexia during labour (defined as ≥38.2 **°**C with epidural, without epidural: ≥38 **°**C), rate of 3rd and 4th degree perineal tears, rate of uterine rupture, estimated volume of blood loss at delivery and postpartum, postpartum blood transfusion, the need for evacuation of retained placenta, use of antibiotics during labour, postpartum infection (defined as two confirmed maternal temperatures of ≥38 °C at least 4 h apart), urinary retention.Fetal/Neonatal: Death, non-reassuring fetal heart rate pattern in labour, birth weight, fetal scalp pH values, Apgar score at 1 and 5 min, umbilical cord arterial pH and blood gas values, antibiotic treatment, hyperbilirubinaemia, rate of admission to neonatal intensive care unit (NICU), or any need for resuscitation (bag and mask or intubation, time to onset of spontaneous ventilation).Breastfeeding (successful establishment and duration of exclusive breastfeeding)Birth experience and patient satisfaction 4 weeks postpartum (Childbirth Experience Questionnaire, CEQ1 [15])

All outcome data will be registered in an eCRF (see Additional file 1) designed for the trial using the REDCap database (including range checks for data values and double entry for primary outcome and selected secondary outcomes). The data collection form can be obtained by contacting the corresponding author.

For participants who discontinue or deviate from the trial protocol all of the above outcomes are still to be collected if available.

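### Fetal scalp pH exists only for fetuses sampled in labour, so testing it between arms is not a randomised comparison and is liable to selection bias

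*Protocol article*

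**What the plan says.** The section Secondary outcomes lists, among the fetal and neonatal items, "non-reassuring fetal heart rate pattern in labour, birth weight, fetal scalp pH values". The item at issue is "fetal scalp pH values": the values themselves, not the proportion sampled or the proportion with a low result. Umbilical arterial pH is listed separately in the same sentence.

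The section Power calculation and statistical analysis sets the intention-to-treat principle and one rule for continuous secondary outcomes: "we will assess differences between groups using the student’s t-test, and with a non-parametric Mann-Whitney U test if the data are non-Gaussian". For the others it says: "Categorical secondary outcomes will be assessed in the same way as the primary outcome". Scalp pH is neither exempted nor given an analysis set.

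The Background reports that in the pilot the discontinued group had "statistically significant fewer cases of postpartum haemorrhage, uterine tachysystole, and non-reassuring fetal heart pattern". Side effects and risks expects maternal and neonatal complications to be lower in that group.

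Secondary outcomes also contains "any need for resuscitation (bag and mask or intubation, time to onset of spontaneous ventilation", where the ventilation time stands inside the brackets of the resuscitation item.

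**The concern.** Randomisation makes the two arms comparable as whole groups. It does not make comparable the fetuses in each arm who happen to be sampled, because the decision to sample can follow the start of study medication and responds to fetal condition. If discontinuation reduces the signs that prompt sampling, fewer fetuses are sampled in that arm, and those who are sampled may be a more compromised selection. Their mean pH could then look worse although treatment has no effect on pH, or a real benefit could be masked. A test on the values would still appear under an intention-to-treat heading, and a reader would take it as a randomised comparison.

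**Working it through.** **1. Does the plan's wording lead to this test?** Scalp pH is a continuous measurement, is named as a secondary outcome, and falls under the t-test or Mann-Whitney rule. A fetus that was not sampled has no value. Applying the rule as written therefore compares sampled fetuses only. The article does not state this restriction; it follows from the nature of the measurement.

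**2. Are the conditions for bias plausible?** Bias needs two things: sampling affected by treatment, and sampling related to the pH value. The pilot result on heart-rate patterns and the expectation of fewer complications make the first plausible. Sampling in response to fetal condition makes the second plausible. Neither is quantified in the article.

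**3. How large could it be?** The plan has no figure of its own on this point to reproduce. The only input from the article is 600 women per arm. The rest is assumed: pH SD σ = 0.06, no treatment effect on pH, and a latent distress score U (standard normal) with correlation ρ in size with pH, higher distress going with lower pH. In each arm the most distressed fraction p is sampled.

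With z the upper-p normal quantile, λ = φ(z)/p and k = λ(λ − z):

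- mean pH among sampled = μ − σρλ
- variance among sampled = σ²(1 − ρ²k)
- false difference (discontinued minus continued) d = −σρ(λ_D − λ_C)
- SE = σ√[(1 − ρ²k_C)/(600p_C) + (1 − ρ²k_D)/(600p_D)]
- rejection rate = Φ(|d|/SE − 1.96) + Φ(−|d|/SE − 1.96)

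The mean μ and the SD σ cancel from the rejection rate, which depends only on the shares, ρ and the 600.

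Worked case, 25% continued v 15% discontinued, ρ = 0.7: λ_C = 1.2711, λ_D = 1.5544, k_C = 0.7584, k_D = 0.8051.

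- d = −0.06 × 0.7 × (1.5544 − 1.2711) = −0.0119
- SE = 0.06 × √[(1 − 0.49 × 0.7584)/150 + (1 − 0.49 × 0.8051)/90] = 0.00627
- |d|/SE = 1.90, so the rejection rate is 47.5%

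| Sampled, continued v discontinued | False difference, ρ = 0.3 / 0.5 / 0.7 | Rejection at nominal 5% |
|---|---|---|
| 20% v 20% | 0 / 0 / 0 | 5.0% / 5.0% / 5.0% |
| 12% v 10% | −0.0016 / −0.0026 / −0.0037 | 5.3% / 5.9% / 7.4% |
| 8% v 6% | −0.0023 / −0.0038 / −0.0053 | 5.4% / 6.2% / 8.2% |
| 10% v 7% | −0.0029 / −0.0049 / −0.0069 | 5.7% / 7.4% / 11.5% |
| 20% v 15% | −0.0028 / −0.0046 / −0.0065 | 6.4% / 9.5% / 16.8% |
| 25% v 15% | −0.0051 / −0.0085 / −0.0119 | 10.1% / 22.0% / 47.5% |

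Simulating the 25% v 15% model with 4,000 trials per setting gives 10–11%, 21–24% and 47–48%. With ρ = 0 there is no bias at any shares. A wider assumed gap goes further: 40% v 20% with ρ = 0.6 gives about 78%.

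**4. Can a benefit be masked?** With 25% v 15% and ρ = 0.5, a true gain of +0.010 would be estimated at 0.010 − 0.0085 = +0.0015. It would be detected in about 6% of trials, against 36% if both arms were sampled at 25%.

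**The case against.** The strongest reply is that the article never says scalp pH is compared only in sampled fetuses, and never names it in the analysis section. The analysis set for one item in a long list is the kind of detail an article leaves to the full protocol or SAP. Part of this stands: an unseen SAP may deal with it, and a missing definition alone would be no finding. But the article does state a test rule, and applied to an outcome it names, that rule gives a comparison that is not randomised.

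A reader might infer that the comparison *is* biased. The documents do not support that. They give no sampling rates and no rule linking heart-rate findings to scalp sampling; the section Complications says only that such findings lead to reducing or stopping the infusion. The step from a 200-woman pilot's heart-rate result to unequal sampling is an inference. Side effects and risks also expects more persistent failure to progress with discontinuation (8–46% v 3–17%), and Dystocia allows open-label oxytocin then, which dilutes the contrast. With nearly equal shares the inflation is small.

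A reader might also put "time to onset of spontaneous ventilation" on the same footing. That is weaker. It sits in brackets under the resuscitation item, which reads as a yes/no outcome to be compared in all newborns. It may be only a descriptor, or a time recordable for every newborn.

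Finally, a reader might infer that the trial's neonatal safety conclusions are at risk. They do not rest on scalp pH. Umbilical arterial pH, Apgar score, NICU admission, resuscitation and death are all listed and are not confined by definition to sampled fetuses. The abstract names umbilical arterial pH and Apgar score, not scalp pH.

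**Conclusion.** The point holds for scalp pH, as a liability to bias and not as a demonstrated bias. Following the article as written means testing a subset selected after randomisation, and the article's own pilot makes unequal selection by arm plausible. The size cannot be computed from the documents. Under assumed shares and correlations the type I error lies between about 5% and nearly 50% (25% v 15%, correlation 0.7), with a false difference of at most 0.012 pH units over the tabulated settings; more extreme assumptions give more. In this model the arm with fewer samples looks worse, but that direction is also a consequence of the assumptions. For time to spontaneous ventilation the point applies only if it is analysed as a time among resuscitated newborns. One minor secondary outcome is affected; the primary outcome and the sample size are not.

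**What to change.** In Secondary outcomes and in Power calculation and statistical analysis:

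- Make scalp sample taken (yes/no) the outcome compared between arms, with all randomised women as the denominator, using the method already stated for categorical outcomes.
- Report scalp pH values descriptively, with the number sampled per arm and no between-arm test.
- Name umbilical arterial pH, already listed, as the acid-base comparison.
- If an outcome of sampled with low pH over all randomised is wanted, label it a composite of sampling and result. An unsampled fetus does not necessarily have a normal pH, since a compromised one may be delivered at once without sampling, and the composite also varies with willingness to sample. The article gives no threshold, so one would have to be pre-specified.
- State whether time to spontaneous ventilation is analysed as a time among resuscitated newborns. If so, report it descriptively as well and keep the yes/no resuscitation outcome for the test.

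The cost is a change of wording; whether a sample was taken can be derived from the scalp pH data already to be recorded. The one loss is the formal test on continuous scalp pH.
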